### Ethical Considerations

The study was approved by the Nazarbayev University Institutional Research Ethics Committee in July 2024 (Multimedia Appendix 4), and secured funding in August 2024, after a peer-reviewed process (Multimedia Appendix 5).

One of the physicians at the dialysis center will explain the aim of the study and the echocardiographic procedure. Written informed consent will be obtained from all participants before the procedure (Multimedia Appendix 6).

Participation in the study is on a voluntary basis, thus no compensation will be offered to patients.

Important protocol modifications during the study will be submitted to the Institutional Research Ethics Committee of Nazarbayev University for approval.

## Results

### Overview

At least 323 patients are required to estimate the incidence of cardiovascular events with 95% CI and a 5% margin of error. Data collection is scheduled to occur between January 1, 2025, and June 30, 2025. As of March 18, 2025, a total of 32 participants have been recruited, who underwent echocardiogram before and after the HD session. Data analysis is planned to start in April 2025 and continue through June 2026, with certain data being collected concurrently during the analysis phase. The publication of study outcomes is tentatively projected in Winter 2027.

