**Methods:**

A 2D transthoracic echocardiogram will be performed before and after a HD session in patients with end-stage renal disease. We target to enroll 323 patients. Images will be analyzed with advanced software based on speckle-tracking, able to reconstruct the pressure-volume loop. From the pressure-volume loop, arterial (Ea) and ventricular (Ees) elastance will be derived. VAC will be calculated as the Ea/Ees ratio. Patients will be followed up for 18 months. Primary endpoints will be a composite of all causes of death, nonfatal myocardial infarction, and hospitalization due to worsening heart failure.

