**Results:**

The study received funding in August 2024, with patients’ enrollment scheduled to take place from January 1 to June 30, 2025. Data analysis will start in April 2025 and is expected to continue until June 2026. The findings of the study are tentatively planned for publication in the winter of 2027.

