**2025**													
	Patient recruitment, informed consent, and data collection from eligible participants	✔	✔	✔	✔	✔	✔	✔	✔	✔	✔	✔	✔
	Data analysis (VAC)				✔	✔	✔	✔	✔	✔	✔	✔	✔
	1-year follow-up			✔	✔	✔	✔	✔	✔	✔	✔	✔	✔
	Manuscript preparation: (VAC)							✔	✔	✔	✔	✔	✔

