### Sample Size

The sample size was calculated based on 95% CI, margin of error 5%, and estimated incidence of cardiovascular events 30%, as follows:

[figure not shown]

where N is the sample size, 
[figure not shown]
 is a critical value from the standard normal distribution corresponding to the desired 95% CI (1.96), *P* is the proportion of estimated incidence (0.3), and E is the desired margin of error (0.05) [16].

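### Enrolment closes on 30 June 2025 in the abstract but runs to December 2025 in Table 1, and at the reported accrual the June close cannot credibly deliver 323 patients or the ±5-point margin

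*Protocol article*

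**What the plan says.** **Target.** The abstract gives the size: "We target to enroll 323 patients". The Sample Size section derives it from a 95% interval, "margin of error 5%, and estimated incidence of cardiovascular events 30" per cent. The Results overview repeats it as a minimum: "At least 323 patients are required to estimate the incidence of cardiovascular events with 95% CI and a 5% margin of error".

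**Window, first statement.** The abstract's Results paragraph has "enrollment scheduled to take place from January 1 to June 30, 2025". The Results overview gives the same dates under another name: "Data collection is scheduled to occur between January 1, 2025, and June 30, 2025".

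**Window, second statement.** Table 1 has a 2025 row labelled "Patient recruitment, informed consent, and data collection from eligible participants", ticked from January to December.

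**Progress.** The Results overview says: "As of March 18, 2025, a total of 32 participants have been recruited".

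**Later dates.** Expected Outcomes sets follow-up at 18 months. Table 1 ends final data collection in March 2026 and outcome analysis in June 2026.

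**The concern.** Two problems meet here. The first needs no assumption: the article gives two closing dates for enrolment, six months apart. The second is that the accrual count sits beside a required size that the earlier closing date looks unable to produce. By 18 March the study had 32/323 = 10% of its target with 77/181 = 43% of the January-to-June window gone.

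The sample size rests wholly on the precision of an estimated event incidence. If enrolment closes on the calendar with far fewer patients, the stated ±5 points is lost and the prognostic analysis has correspondingly fewer events. The choice of window also decides when the last patient completes 18 months, and so when outcomes can be analysed.

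**Working it through.** **Inputs.** Target 323, P = 0.30, E = 0.05 and z = 1.96 (Sample Size; Results overview). 32 recruited by 18 March 2025 (Results overview). Closing dates 30 June 2025 (abstract) and 31 December 2025 (end of the Table 1 row). The formula image is not legible in the text, so the usual single-proportion formula is used.

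**1. The plan's own figure.** N = z²P(1−P)/E² = 1.96² × 0.3 × 0.7 / 0.05² = 322.7, rounded up to 323. It reproduces, so the size is correctly calculated for its stated purpose.

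**2. Average pace so far.** 1 January to 18 March is 77 days inclusive. 32/77 = 0.416 per day, or 2.9 per week.

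**3. Pace now required.** 323 − 32 = 291 patients remain.
- To 30 June (104 days): 291/104 = 2.80 per day, and 2.80/0.416 = 6.7 times the average so far.
- To 31 December (288 days): 291/288 = 1.01 per day, 2.4 times.

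**4. Projection at constant pace from 1 January (assumption).** Exact 95% Poisson limits on a count of 32 are 21.9 to 45.2. The margin is 1.96 × √(0.21/n).

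| Close | Days | Projected n | Poisson limits | Margin at projected n |
|---|---|---|---|---|
| 30 June | 181 | 32 × 181/77 = 75 | 51 to 106 | ±10.4 points |
| 31 December | 365 | 32 × 365/77 = 152 | 104 to 214 | ±7.3 points |

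**5. Sensitivity to a later first patient.** The date is not given, so it is varied, with the pace constant from that date.

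| First patient | Days to 18 March | Pace per day | n by 30 June | n by 31 December |
|---|---|---|---|---|
| 1 January | 77 | 0.416 | 75 | 152 |
| 1 February | 46 | 0.696 | 32 + 0.696 × 104 = 104 | 32 + 0.696 × 288 = 232 |
| 1 March | 18 | 1.778 | 32 + 1.778 × 104 = 217 | 32 + 1.778 × 288 = 544 |

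At 217 patients the margin is 1.96 × √(0.21/217) = 6.1 points.

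Break-even start dates:
- For June, 32/2.80 = 11.4 days, so all 32 would have to have entered in roughly the last 11 days before the count.
- For December, 32/1.01 = 31.7 days, so a first patient after about mid-February suffices.

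**6. Follow-up.** Eighteen months after 30 June 2025 is the end of December 2026; after 31 December 2025 it is the end of June 2027. Both fall after Table 1's final data collection (March 2026). The first falls after the end of outcome analysis (June 2026), and the second a year after it.

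**7. Event counts, with the rate stated.** The annual rates in Expected Outcomes sum to 0.10 + 0.0039 + 0.058 = 0.1619. Treated as constant, additive hazards, they give 1 − exp(−0.1619 × 1.5) = 21.6% at 18 months, against the 30% in Sample Size. With 75 patients followed for the full 18 months, that is about 16 events at 21.6% or about 23 at 30%. With 152 it is about 33 or about 46.

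**The case against.** The strongest reply is that 32 patients by mid-March is a report on conduct, not a fault in the plan. New single-centre studies start slowly, the article lists measures against refusal, and one count without a start date cannot establish a rate. This stands in part. It removes any firm claim about December and any firm date for reaching 323. It does not rescue June, where a first patient as late as 1 March still leaves the study about 100 short.

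A second reply is that the Table 1 row combines recruitment with data collection, so its later ticks may mean only data collection; the Results overview also allows some data to be collected during analysis. That does not reconcile the dates, because the row names recruitment and consent and the abstract ties 30 June to enrolment itself.

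A third reply is that the first objective is the paired change in coupling, to which a margin on event incidence is irrelevant. This stands. With 75 pairs, a paired t test has 80% power for a standardised change of about 0.33, so that comparison remains workable.

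A reader might also infer that too few events would remain for a multivariable Cox model. The article does not support this: Statistical Analyses names a Cox model but no multivariable model or covariate list.

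**Conclusion.** The conflict between the two enrolment windows is certain. The shortfall at a 30 June close is robust: about 75 patients (51 to 106) and ±10.4 points at a constant pace from 1 January, and about 217 and ±6.1 points with a first patient on 1 March. The stated 323 and ±5 points are not credible for that window.

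It would be tempting to conclude that neither window can deliver 323. The documents do not support that. The December projection of about 152 (104 to 214, about ±7.3 points) depends on a constant pace from 1 January; if enrolment began after about mid-February, 323 is within reach at constant pace. The Poisson limits reflect only chance variation in the count, not a change of pace.

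The consequence falls on the incidence estimate and the prognostic objective, much less on the paired comparison. The figure of 323 is itself correctly computed.

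**What to change.** 1. State one enrolment window, identically in the abstract, the Results overview and Table 1, and give the date of the first enrolment.
2. Choose one stopping basis. Either end enrolment when 323 is reached and give a projected date, or keep the calendar close and restate the expected size and margin as a range for that window. At constant pace from 1 January the ranges would be 51 to 106 patients for June and 104 to 214 for December; revise them once the first-enrolment date is known.
3. Move final data collection and outcome analysis in Table 1, and the analysis dates in the abstract and Results, so that the last patient's 18 months fit: about December 2026 for a June close, June 2027 for a December close. If enrolment ends on the count, add 18 months to the projected date.
4. If event counts are quoted, give the rate and assumptions with them, and say whether the 30% of Sample Size or the summed rates of Expected Outcomes apply.

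The cost is wording and a revised timetable. Restating the precision requires no added patients, but makes it less favourable. Keeping 323 preserves the margin and probably means a later end to the study.

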## Discussion

### Principal Findings

Data on the value of VAC in patients on HD are scanty and controversial. Moreover, no research on this topic has been conducted in the Republic of Kazakhstan. The results of this study will provide insights into the hemodynamic changes induced by HD in patients with ESRD and will improve the understanding of the pathophysiological events induced by acute volume depletion. The prognostic value of HD-induced VAC changes will be also assessed at follow-up.

### Comparison to Previous Work

The association between myocardial and arterial function markers has been used to describe and quantify VAC in hypertension [21-23], diabetes [24], and inflammatory diseases [25]. More specifically, combined ventricular and arterial stiffening has been demonstrated in patients with heart failure with preserved ejection fraction (HFpEF) [26]. In patients with heart failure, abnormal VAC is implicated in the pathophysiology of left and right heart clinical deterioration [27]. In addition, different patterns of abnormal VAC are recognized in heart failure with reduced ejection fraction versus HFpEF. The results of these studies suggest that in hypertension and diabetes, there is a close link between arterial stiffness and myocardial deformation, which appears to be a harbinger of HFpEF if left untreated. In addition, there is evidence that treatment options may improve both myocardial dysfunction and vascular stiffness and thus improve VAC. Systemic inflammatory processes and oxidative stress may cause an increase in arterial stiffness (leading to an increase in Ea) in parallel to myocardial stiffening (causing an increase in Ees), while anti-inflammatory treatment improves arterial stiffness in parallel with myocardial stiffness contributing to the reversal of ventricular-arterial decoupling.

VAC assessment has prognostic value in several clinical scenarios. Valvulo-arterial impedance can specifically describe the hemodynamic consequences of aortic stenosis and provide prognostic information in patients with aortic stenosis even when asymptomatic [28]. There is also evidence that VAC is associated with outcomes in patients with sepsis or after myocardial infarction [29,30].

In patients with renal dysfunction, increased arterial stiffness coupled with a matched increase in ventricular stiffness has been reported [31,32]. These findings have important hemodynamic consequences as a stiff heart-arterial system generates more systolic pressure changes for a given stroke volume.

Sasso et al [33] evaluated 15 patients on HD. They concluded that HD influences both Ees and Ea/Ees ratio acutely, although this effect seems due only to the acute reduction in preload and blood pressure, without any clinically significant effect on intrinsic LV contractility and VAC. In a study on 234 HD patients, Obokata et al [34] found that Ea/Ees ratio was independently associated with adverse outcomes, providing an incremental prognostic value over the clinical score and left ventricular ejection fraction. Recently, Zuo et al [35] used an approach similar to ours (pre- and posthemodialysis assessment of VAC). They concluded that VAC is a reliable index for stratifying the risk of cardiovascular diseases in HD patients.

### Strengths and Limitations

The approach we are planning to use in this study allows a noninvasive assessment of the cardiovascular efficiency and the changes induced by volume changes during HD in patients with ESRD. The endocardial borders, evaluated by echocardiographic speckle tracking, can be used directly as input to the present model to provide a noninvasive assessment of VAC. Using standard echocardiographic images and advanced image analysis, we will be able to evaluate the heart-arterial system interaction from the VAC. We believe that, using this approach, a comprehensive analysis of the hemodynamic effects of volume changes induced by HD will be feasible. This will allow a better understanding of the pathophysiological changes induced by HD, with the potential of tailoring the optimal dialysis modalities and identifying those patients who are at higher risk of LV remodeling and future cardiovascular events.

Some challenges of this approach can be anticipated. First, echocardiographic image quality may affect proper visualization and tracking of the LV endocardial border. Second, a low frame rate can hamper the temporal resolution of the method. Finally, inter- and intraobserver reliability should be high to exclude changes due to variability.

### Future Directions

Further research should investigate whether modifying VAC through targeted interventions could improve clinical outcomes in HD patients. Expanding the study to larger, multicenter cohorts would enhance the generalizability of our findings. In addition, incorporating advanced imaging techniques to assess VAC dynamically over time may provide deeper insights into its prognostic role in patients undergoing chronic HD.

### Dissemination Plan

The final results will be presented at the main international nephrology and cardiology meetings and conferences. The development and findings of the project will be reported in relevant international journals.

### Conclusions

In conclusion, this research protocol outlines the process of noninvasive assessment of VAC before and after a HD session in patients with ESRD. The methodology we are applying does not require complex and sophisticated tools apart from the analysis software. We believe this approach will provide additional information to the relevant stakeholders and assist other researchers in developing similar studies in different clinical settings.

## Data Availability

The datasets generated or analyzed during this study are available from the corresponding author on reasonable request.

## Appendix

Multimedia Appendix 1 Explanation of the echocardiographic exam in three languages (Kazakh, Russian and English). This will help patients to understand the nature of the procedure.

Multimedia Appendix 2 Case report form used in the study.

Multimedia Appendix 3 SPIRIT (Standard Protocol Items: Recommendations for Interventional Trial) checklist.

Multimedia Appendix 4 Approval of the study from the Nazarbayev University Institutional Research Ethics Committee (IREC).

Multimedia Appendix 5 Peer review report from the Ministry of Sciences and Higher Education of the Republic of Kazakhstan.

Multimedia Appendix 6 Informed consent.

## Abbreviations

Ea: arterial elastance
EDPVR: end-diastolic pressure-volume relationship
Ees: ventricular elastance
ESPVR: end-systolic pressure-volume relationship
ESRD: end-stage renal disease
HD: hemodialysis
HFpEF: heart failure with preserved ejection fraction
ICC: Interclass correlation coefficients
LV: left ventricle
P-V: pressure-volume
SPIRIT: Standard Protocol Items: Recommendations for Interventional Trial
VAC: ventriculo-arterial coupling
